### Randomization

2.5

According to the random number table generated by the computer, the participants will be randomly assigned to the 2 groups. The randomized allocation sequence will be performed by a researcher who will not be involved in the recruitment, evaluation, or training of patient. Random numbers will be placed in sealed opaque envelopes to blind the group allocation.

## Interventions

3

All participants will be treated with routine treatment and nursing according to their specific condition. The experimental group will be combined with sitting and lying Liuzijue on the basis of the control group.

### The control group

3.1

Participants in the control group will be treated with standard drugs of AECOPD, including bronchodilator (short-acting β 2 agonist and anticholine), oral prednisone (40 mg/d, for 5 days), and antibiotics (amoxicillin-clavulanic acid, respiratory quinolone, macrolides) according to the results of sputum culture if necessary. The range of oxygen concentration in NIV needs to be controlled. It's necessary to adjust the oxygen concentration according to the patient's tolerance and blood oxygen saturation. In addition, oxygen saturation need to be maintained at 90% to 94% for avoiding the occurrence or aggravation of CO_2_ retention and/or respiratory acidosis. Routine respiratory function exercise including lip contraction breathing and abdominal breathing. The routine nursing including many aspects, such as condition observation, respiratory care (pay attention to sputum drainage, active expectoration, etc), diet nursing (eating high-quality protein, high vitamins, low-fat diet, more light and digestible food, more water, and supplement essential diet or high intravenous nutrition who cannot eat anything), psychological nursing (giving psychological comfort and spiritual support) and health education, etc.

### The experimental group

3.2

On the basis of the control group, participants in the experimental group will practice sitting and lying Liuzijue once every morning and evening, 30 minutes each time, for a total of 3 months. Before the official start of the experiment, 2 members of the research group need to be trained in skills and methods. After successfully passing the examination, they would conduct action guidance and training to the participants. The teaching time of patients should be controlled within 5 days, and they should be assessed on the last day. After the patients have correctly mastered the steps, essentials and matters needing attention of sitting and lying Liuzijue, they will formally enter the experiment.

Sitting and lying Liuzijue exercise begin immediately after the appearance of the lung infection control window. Exercise once every morning and evening, each time for 30 minutes, for a total of 3 months. In the process of exercise, the participants need to take off the NIV mask and use nasal catheters to inhale oxygen. The pulse oxygen saturation meter will be used to closely monitor the changes of heart rate and fingertip oxygen saturation. Take continuous exercise and intermittent exercise according to the tolerance of participants. The next day, ask the participants about their physical recovery and observe their breathing and heart rate during the entire exercise to confirm whether the current exercise intensity is appropriate.

All participants use reverse abdominal breathing, exhale first and then inhale. Read when they exhale, lift the anus and contract the kidney at the same time (abdomen and buttocks, urethral orifice, and anal micro-lift). When inhaling, the lips are gently closed, the tongue is against the upper jaw, the whole body is relaxed, the lower abdomen is naturally raised, and the air is naturally inhaled. After reading each word 6 times, using natural breathing, tongue against the palate (cis-abdominal breathing can also be used). The function is to adjust breathing, restore nature, and take a short rest. The detailed steps are shown in Fig. 3.

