### Design

2.1

This study is a clinical randomized controlled trial. Sixty four AECOPD participants with NIV will be conducted in the Hospital of Chengdu University of TCM (Chengdu, China). Participants will be recruited through a recommendation by the respiratory clinician. The participants will be informed of the benefits and risks of the study in detail. After obtaining written informed consent, eligible participants will be randomly assigned to the experimental group and control group in a ratio of 1:1. To prevent design bias, we will follow the Consolidated Standards of Reporting Trials statement^[17]^ and the Standard Protocol Items: Recommendations for Interventional Trials (SPIRIT) 2013 statement.^[18]^ The study procedure is shown in Fig. 1 and the time points of the study is shown in Fig. 2.

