### Outcome measures

3.4

The primary outcomes are the pulmonary function test (FEV_1_%, FEV_1_/FVC, and FVC) and 6-minute walking test (6MWT). The secondary outcome measures include blood gas parameters (PH, PaCO2, PaO2), the mMRC, Hospital Anxiety and Depression Scale (HADS), and St·George Respiratory Questionnaire (SGRQ). Baseline data will be collected before intervention. Outcome indicators will be collected at the 13th week.

The measurement of pulmonary function will be carried out by the same pulmonary function technician in the respiratory department. Before the test, the participants need to take a rest quietly for 10 minutes, then inhaled the bronchodilator salbutamol 200 μg. The arterial blood will be collected by the nurses in the department for blood gas analysis. 6MWT will be carried out by trained team members. Before the test, the participants need to take a rest for 10 minutes, and their blood pressure, pulse, and blood oxygen saturation will be measured. Carry a portable pedometer and walk as fast as possible. At the end of time, blood pressure, pulse, and blood oxygen saturation will be measured again, and the walking distance will be recorded. All the scales involved in this study will be completed by 3 specialized researchers who had received professional training and passed the examination.

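### Section 3.2 sets a mastery condition for formal entry that applies to one arm and falls after randomisation; the handling of those who do not meet it, and the start of the 13-week clock, are not stated

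*Protocol article*

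**What the plan says.** Section 2.1 (Design) places allocation directly after consent: "After obtaining written informed consent, eligible participants will be randomly assigned to the experimental group and control group in a ratio of 1:1".

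Section 3.2 (The experimental group) adds a teaching phase: "The teaching time of patients should be controlled within 5 days, and they should be assessed on the last day". It continues: "After the patients have correctly mastered the steps, essentials and matters needing attention of sitting and lying Liuzijue, they will formally enter the experiment". The next paragraph gives another starting point: "Sitting and lying Liuzijue exercise begin immediately after the appearance of the lung infection control window". The course is defined as: "Exercise once every morning and evening, each time for 30 minutes, for a total of 3 months".

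Section 3.1 (The control group) has its own breathing training, "Routine respiratory function exercise including lip contraction breathing and abdominal breathing", but describes no teaching period, assessment or entry condition.

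On timing, section 3.4 (Outcome measures) says "Baseline data will be collected before intervention" and "Outcome indicators will be collected at the 13th week". Neither sentence names the date from which time is counted.

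**The concern.** Only patients allocated to Liuzijue are taught it, so the mastery condition must fall after randomisation and in one arm. The introduction describes these patients as often severely breathless, with fatigued respiratory muscles and poor early compliance. Those who cannot learn the exercise within 5 days are plausibly the sicker ones. If they are left out of the experimental arm and their counterparts remain in the control arm, the groups are no longer the ones that randomisation formed, and the experimental mean rises without any treatment effect.

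The second issue is timing. Patients are recovering from an acute exacerbation, so the outcome may depend on when it is measured. Controls have no event that corresponds to mastery. A clock that starts at formal entry would therefore have different origins in the two arms.

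**Working it through.** The plan gives no figure for this point (no expected failure rate, no day 0), so there is nothing to reproduce. The 6-minute walking test assumptions in section 2.3 serve as the yardstick.

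**Inputs from section 2.3**
- Planned difference: 486.7 − 442.5 = 44.2 m.
- Pooled SD: √((61.5² + 67.3²)/2) = √4155.77 = 64.47 m.
- 26 patients per arm before the dropout allowance, taken as given and used only for the type I error illustration.

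**Selection through the mastery condition**

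Let f be the share of the experimental arm that does not reach mastery, and g the gap in walking distance, in SDs, between those who do and those who do not. Both are assumed; the documents give neither. If non-masterers are left out and there is no true effect, the mean of those remaining exceeds the mean of the whole randomised arm by f × g × SD.

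| f | g = 0.5 | g = 1.0 | Share of 44.2 m | Two-sided type I error, 26 per arm |
|---|---|---|---|---|
| 5% | 1.6 m | 3.2 m | 4-7% | 0.051-0.054 |
| 10% | 3.2 m | 6.4 m | 7-15% | 0.054-0.064 |
| 20% | 6.4 m | 12.9 m | 15-29% | 0.064-0.109 |

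The corners are 0.05 × 0.5 × 64.47 = 1.6 m and 0.20 × 1.0 × 64.47 = 12.9 m. The type I error comes from a non-central t distribution with 50 degrees of freedom and non-centrality f × g / √(2/26), at a nominal two-sided 5%. If everyone is followed and analysed in the allocated arm, nobody is removed and this bias is zero.

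**The 13-week clock**

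Thirteen weeks are 13 × 7 = 91 days.
- *Counted from formal entry:* experimental patients are measured up to day 91 + 5 = 96 after randomisation, against day 91 for controls counted from randomisation. The gap is larger if waiting for the infection control window also delays entry. As an illustration only, an assumed natural gain of 50-100 m spread evenly over 91 days would give 5/91 × 50 = 2.7 m to 5/91 × 100 = 5.5 m extra; less if recovery slows with time.
- *Counted from randomisation:* both arms are measured at the same time. Up to 5 days of teaching leave 91 − 5 = 86 days of formal exercise, up to 5/91 = 5.5% less. If 3 months means 12 weeks (84 days, also an assumption), teaching plus exercise ends by day 5 + 84 = 89, and the course fits.

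**Start of exercise**

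Section 3.2 ties the start to mastery in one paragraph and to the infection control window in the next, and does not say how the two relate.

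**The case against.** The best defence is that formal entry in this translated text means only the start of the formal exercise phase. Several things support it. Section 2.2 places entry to the research group after consent is signed. Section 3.2 already calls those being taught participants. Section 2.4.4 does not list a failed assessment among the termination and withdrawal criteria, although it does list poor compliance. The inclusion and exclusion criteria also require patients who can communicate normally and exclude those intolerant to exercise, so failure may be rare. Rules for analysis sets are commonly left to a full protocol or analysis plan, which is not shown.

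Much of this stands, and it rules out four stronger readings that a reader might infer:
- *That patients who fail are excluded.* No sentence says so; it is one reading of the wording.
- *That the week-13 visit shifts.* The text gives no day 0, and the figures with the study procedure and time points are not available here and may define it.
- *That both effects necessarily favour Liuzijue.* Under a clock from randomisation, the visits coincide and the experimental arm may have slightly less exercise, which would not favour it.
- *That the bias cannot be removed in the analysis.* Full follow-up analysed as randomised removes the selection.

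Nor are the two start triggers a necessary contradiction: teaching could be finished before the window appears. But the text does not say this.

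What the defence does not remove is the rule itself. A condition for entry, in one arm and after randomisation, is stated in the text, and nothing in the document says that those who do not meet it are kept, followed and analysed. Staff could follow it literally.

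**Conclusion.** The concern holds as a badly fixed entry rule that leaves a risk of selection open; it does not show that bias will occur. If non-masterers are left out, the bias favours Liuzijue and would be about 1.6-12.9 m, or 4-29% of the planned 44.2 m. That range rests wholly on the assumed failure share (5-20%) and gap (0.5-1 SD). At 5-10% failing, the type I error stays between 0.051 and 0.064; only the extreme corner reaches 0.109.

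The timing issue is smaller and conditional: a measurement up to 5 days later in the experimental arm, or an exposure up to 5 days shorter, depending on an origin that the text shown does not give. Both issues are cheap to close before recruitment and hard to repair afterwards if non-masterers have not been followed up.

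**What to change.** In sections 3.2 and 3.4, state that:
- every patient is in the trial from randomisation, whether or not the exercise is mastered;
- teaching is part of the experimental intervention;
- non-mastery is recorded as a measure of adherence, and the patient is followed and analysed in the allocated arm;
- baseline and the week-13 visit are anchored to the randomisation date in both arms, with one common visit window.

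Reconcile the two statements in section 3.2 on when exercise starts, so that the order of teaching, assessment, infection control window and formal exercise is clear. Which trigger applies is for the investigators to settle.

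The cost is protocol wording and visit scheduling. The one statistical downside is slight dilution of the effect estimate, because patients who never master the exercise count in the experimental arm.

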**Figure 3 F3:**
[figure not shown]
Main characteristics of sitting and lying Liuzijue.

When the participant is discharged from the hospital, we will distribute sitting and lying Liuzijue exercise manual, video, and intervention diary. At the same time, communicate, guide, and supervise through telephone and WeChat groups.

### Compliance

3.3

Keep communication effectively with participants and establish a good relationship. Inform participants the importance of practicing sitting and lying Liuzijue for disease recovery. During hospitalization, members of the research group will guide and supervise participants every day. When the participants are discharged from hospital, distribute “intervention diary” and conduct guidance and supervision through telephone and WeChat groups. If the participants are not motivated enough during the trial, they would be encouraged and the frequency of supervision would be increased. In the process of intervention, participants can share and communicate with each other through WeChat groups for promoting compliance.

### Outcome measures

3.4

The primary outcomes are the pulmonary function test (FEV_1_%, FEV_1_/FVC, and FVC) and 6-minute walking test (6MWT). The secondary outcome measures include blood gas parameters (PH, PaCO2, PaO2), the mMRC, Hospital Anxiety and Depression Scale (HADS), and St·George Respiratory Questionnaire (SGRQ). Baseline data will be collected before intervention. Outcome indicators will be collected at the 13th week.

The measurement of pulmonary function will be carried out by the same pulmonary function technician in the respiratory department. Before the test, the participants need to take a rest quietly for 10 minutes, then inhaled the bronchodilator salbutamol 200 μg. The arterial blood will be collected by the nurses in the department for blood gas analysis. 6MWT will be carried out by trained team members. Before the test, the participants need to take a rest for 10 minutes, and their blood pressure, pulse, and blood oxygen saturation will be measured. Carry a portable pedometer and walk as fast as possible. At the end of time, blood pressure, pulse, and blood oxygen saturation will be measured again, and the walking distance will be recorded. All the scales involved in this study will be completed by 3 specialized researchers who had received professional training and passed the examination.

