### Sample size

2.3

The calculation of sample size is based on the main results (6MWT). According to the previous literature,^[19]^ it is estimated that the average score of the control group was 442.5 and the standard deviation was 61.5. After Taiji Qigong exercise, the average of the experimental group was 486.7 and the standard deviation was 67.3. formula for calculating the sample size is as follows: 

At the 5% significance level, a total of 26 patients are needed in each group to achieve 80% power. The estimated dropout rate is 20%, and a total of 32 patients have been included in each group.

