### Statistical analysis

3.6

Two researchers who are not be involved in the recruitment, evaluation, or training of patient will be responsible for entering the data. Statistical analysis will be carried out by using SPSS 24.0 statistical software. If the measurement data accorded with normal distribution, it will be described by mean and standard deviation. If not, it will be described by median and quartile distance. The measurement data will be examined using group *t* tests or non-parametric tests, the count data will be tested using a Chi-square test or Fisher exact probability method, and the grade data will be tested using non-parametric tests. All statistical tests will be bilateral tests and *P* < .05 will be considered to indicate statistical significance.

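### Four co-equal primary measures, each tested at two-sided P < .05 with no hierarchy or success rule, in a trial sized on 6MWT alone

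*Protocol article*

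**What the plan says.** Three sections of the protocol article bear on this point.

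- **Outcome measures (3.4):** "The primary outcomes are the pulmonary function test (FEV_1_%, FEV_1_/FVC, and FVC) and 6-minute walking test (6MWT". That is three spirometry measures plus walking distance, with no order among them and one post-baseline assessment, at week 13. The abstract also gives pulmonary function and 6MWT together as primary.
- **Statistical analysis (3.6):** "All statistical tests will be bilateral tests and *P* < .05 will be considered to indicate statistical significance". The same threshold covers all tests. Nothing here or elsewhere ranks the primaries, divides alpha, or says whether one or all of them must be significant.
- **Sample size (2.3):** "The calculation of sample size is based on the main results (6MWT"). The inputs are 6MWT means and SDs only. No effect or SD is given for FEV1%, FEV1/FVC or FVC.

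**The concern.** The sample size section implies one main outcome. The outcome section and the abstract declare four of equal rank, and the analysis section gives each its own full 5%. A reader cannot tell what result would make the trial positive.

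Two things are at stake. If any single significant primary is enough, the 5% error rate does not apply to the trial's primary conclusion, and an isolated P < .05 on FVC, for example, could be presented as primary success. If all four are required, overall power depends on three spirometry outcomes for which nothing was planned. The Discussion expects the study to confirm improvement in lung function and exercise endurance, the two domains that the four primaries cover, so the choice affects the headline claim.

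**Working it through.** **Inputs from the protocol article**

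- Primary measures: 4 (section 3.4).
- Alpha per test: 0.05, two-sided (section 3.6).
- 6MWT control mean 442.5, SD 61.5; experimental mean 486.7, SD 67.3 (section 2.3).
- 26 evaluable per group for 80% power at 5%, and 32 per group after allowing for 20% dropout (section 2.3).
- Correlations among the four measures: not given. The values below are assumptions.

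**1. The plan's own figure.** Difference = 486.7 − 442.5 = 44.2. Pooled SD = √[(61.5² + 67.3²)/2] = 64.47. The normal-approximation formula is n per group = 2(z_α + z_0.80)² × SD² / difference².

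- One-sided 5%: 2 × (1.645 + 0.842)² × 64.47² / 44.2² = 26.3, rounded up to 27, close to the stated 26.
- Two-sided 5%: 2 × (1.960 + 0.842)² × 64.47² / 44.2² = 33.4, rounded up to 34.

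So the stated 26 is approximately matched only by a one-sided test. This is a separate sample-size issue. It matters here only because it sets the baseline power in step 4.

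**2. False-positive rate if any one of four counts.**

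- Four independent tests: 1 − 0.95⁴ = 0.185.
- Ceiling under any dependence (sum of alphas): 4 × 0.05 = 0.20.
- Four equicorrelated two-sided z tests, by simulation:

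| Assumed common correlation | Chance of at least one false positive |
|---|---|
| 0 | 18.5% |
| 0.3 | 17.4% |
| 0.5 | 15.6% |
| 0.7 | 13.0% |
| 0.9 | 9.4% |

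A more realistic structure lets the three spirometry measures correlate more with each other than with 6MWT. With an assumed 0.5 to 0.8 within spirometry and 0.2 to 0.4 with 6MWT, simulation gives about 14% to 17%.

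**3. False-positive rate if all four must succeed.** It cannot exceed the 5% of a single test, so there is no inflation. Power then cannot exceed that of the weakest of the four, and for three of them the plan gives no effect from which to compute it.

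**4. What a Bonferroni split would cost.** Alpha per test = 0.05/4 = 0.0125. Power for 6MWT from the noncentral t distribution, two-sided, with noncentrality 44.2 / (64.47 × √(2/26)) = 2.47 at 26 per group:

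| Evaluable per group | Power at 0.05 | Power at 0.0125 |
|---|---|---|
| 26 | 68% | 46% |
| 32 (no dropout) | 77% | 57% |

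Restoring 80% at 0.0125 would need 48 evaluable per group by the normal approximation: 2 × (2.498 + 0.842)² × 64.47² / 44.2² = 47.4, rounded up. With 20% dropout that is 48/0.8 = 60 per group, against the planned 32.

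**The case against.** The best defence is that this is a condensed article, and that multiplicity handling is commonly left to a statistical analysis plan that is not shown. The threshold sentence in section 3.6 is generic. That has some force against a complaint that an adjustment method is missing. It does not answer the point, because the article itself names four primaries, itself sets 5% for every test, and itself sizes the trial on one of the four. The mismatch between sections 2.3 and 3.4 is in the text.

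A second defence is that the inflation is conditional, and this stands. A reader might infer that the plan lets any one significant primary carry the trial, and so that its false-positive rate simply is about 18%. The documents do not support that. No success rule is stated, and if all four were required the rate would not be inflated. The 18.5% also needs independence, which is implausible for three measures from one spirometry test, one of them a ratio with FVC as its denominator. Nor is 18.5% the upper limit, which is 20%.

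Third, sizing a trial on one key outcome is common, so the absence of planned power for spirometry is not an error in itself. It becomes a problem only if spirometry has to succeed for the trial to succeed.

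Finally, a reader might blame multiplicity for the gap between 68% power and the stated 80%. That gap comes from the sample-size calculation. Only the fall from 68% to 46% belongs to the Bonferroni split.

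**Conclusion.** The point holds in conditional form. The article fixes four co-equal primaries and a 5% threshold for each, gives no rule for combining them, and treats 6MWT alone as the main result when sizing the trial. Trial success is therefore undefined.

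Under the any-one reading, the primary false-positive rate is about 9% to 18.5% over assumed common correlations from 0.9 to 0, and about 14% to 17% under the more realistic structure assumed above. Each of these values is well above 5%. Under the all-four reading there is no inflation, but power rests on three outcomes with no planned effect. The correlations are assumptions, since the article gives none. That the text does not choose between the two readings is the defect, and it does not depend on those assumptions.

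**What to change.** Before any outcome data are seen, amend section 3.4 and the abstract so that 6MWT distance at week 13 is the sole primary outcome, tested two-sided at 5%. This agrees with the basis already used in section 2.3. For FEV1%, FEV1/FVC and FVC, choose one of two routes and write it down:

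- make them secondary outcomes, reported with estimates and 95% intervals; or
- keep them confirmatory in a stated fixed order, tested only after 6MWT is significant, each step requiring significance at the one before.

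Either route holds the primary error rate at 5% without more patients. The cost is that spirometry, which the abstract and section 3.4 list first, loses its co-equal primary status. The protocol and registry record need amending, and section 2.2 requires renewed ethics approval for any protocol amendment. Data collection does not change.

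Keeping four primaries with a Bonferroni split would also control the error rate, but at the much higher price in power or sample size shown in the working. The gap between 68% and the stated 80% should be resolved separately in section 2.3.
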